#### Fever surveillance**—**laboratory testing

As shown in figure 6, in all three sites, acute samples were tested using a commercial RDT for dengue NS1 and IgM/IgG (Dengue Duo, Standard Diagnostics, Yongin-Si, Korea). Dengue Duo RDT was used on the day of acute illness visit at the site of patient presentation (day 1). The acute and convalescent samples were subsequently tested at a local laboratory using dengue IgM/IgG ELISA (SD Dengue IgM & IgG Capture ELISA, Standard Diagnostics, Yongin-Si, Korea). The serum was separated and stored in 4 aliquots of about 500 µL for various laboratory tests, as indicated in consent documents.

**Figure 6 F6:**
[figure not shown]
Laboratory testing algorithm for dengue. Samples from subjects of the passive fever surveillance would follow these steps of the testing algorithm for confirmation of dengue. *Dengue Duo^®^test is performed on enrolled febrile patients to identify dengue cases for immediate follow-up of dengue-confirmed cases in the cost-of-illness survey. **Selected samples, including those that were found positive by IgM and NS1 on Dengue Duo^®^, as well as those positive by IgM and IgG capture ELISA, will be tested with RT-PCR.

After ELISA testing, samples were shipped to the International Vaccine Institute (IVI) in Korea. Samples with positive results by RDT or ELISA, as well as a small number of samples with negative results, undergo further testing by RT-PCR at the Clinical Immunology Laboratory of IVI. Four DENV serotype-specific real-time RT-PCR assays are used for laboratory confirmation of dengue and serotyping.^38^ The DENV 1–4 RT-PCR assays are carried out in 25 µL reaction mixtures containing 5 µL template RNA, TagMan Fast Virus 1-step mastermix (Applied Biosystems), 0.9 µM of each primer and 0.2 µM probe.^38^ Amplification and detection are performed in a StepOne Plus real-time PCR system, and the baseline and threshold are determined using the auto-baseline and threshold feature in StepOne Software V.2.2.2 (Applied Biosystems). Thermocycling parameters are as follows: reverse transcription at 50°C for 5 min, inactivation at 95°C for 20 s, followed by 45 cycles of fluorescence detection at 95°C for 3 s and annealing at 60°C for 30 s.^38^ A specimen is considered positive if target amplification is recorded within 40 cycles.

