### Study components

#### Fever surveillance—design and methods

To determine burden due to symptomatic dengue in each of the three sites in Burkina Faso, Gabon and Kenya, passive facility-based fever surveillance was implemented in a well-defined catchment area population. In Burkina Faso, the surveillance study was initiated in December 2014 in five selected primary healthcare centres, locally called ‘Centre de Santé et de Promotion Sociale’, in the municipality of Ouagadougou, with a catchment population of 105 000 residents. This project was implemented in collaboration with Centre Muraz in Bobo-Dioulasso, EQUITE sante programme (a collaborative programme between University of Montreal and Action-Gouvernance-Integration-Reinforcement, AGIR, based in Ouagadougou, funded by the Canadian Institute of Health Research) and DVI. In Gabon, the surveillance study was initiated in the ASH serving a catchment population of 130 000 residents in the Moyen-Ogooué and surroundings within Lambaréné, in collaboration with CERMEL and Institute of Tropical Medicine in Tubingen, Germany. In Kenya, the surveillance study was implemented at Ganjoni dispensary, Tudor subcounty Hospital and Coast Provincial General Hospital, serving a catchment population of 70 000 residents in Mombasa, in collaboration with Kenya Medical Research Institute and Ministry of Health of Kenya.

As described in figure 5, both outpatients and inpatients at the designated study facilities, who meet inclusion criteria as mentioned earlier were tested for dengue, first with SD Dengue Duo RDT. Dengue confirmation was done by detection of dengue virus in serum samples using PCR as well as antidengue IgM and IgG antibodies in acute and convalescent serum by ELISA (SD Dengue IgM & IgG capture ELISA tests, Standard Diagnostics, Yongin-Si, Korea).^10 37^ Every consecutive patient meeting inclusion criteria was eligible for enrolment during the study period. Infants<1 year old were not included due to operational limitations, such as difficulty of infantile bleeding.

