**Figure 5 F5:**
[figure not shown]
Patient flow in the fever surveillance. Eligible febrile patients identified and enrolled as study subjects followed these steps to complete participation in the passive fever surveillance. * A small number of those samples that are negative on ELISA or NS1 are tested with PCR to exclude false negative results of the ELISA. CRF, case report form.

In Ouagadougou, Burkina Faso, the fever surveillance was initiated in December 2014 and continued until February 2017 (approximately 2 years). In Lambaréné, Gabon, the fever surveillance was initiated in April 2015 and continued until January 2017 (approximately 1.5 years). In Mombasa, Kenya, the fever surveillance was initiated in March 2016 and continued until May 2017 (15 months).

Among subjects enrolled in the fever surveillance, those who were positive by dengue rapid diagnostic test were offered further enrolment in the cost-of-illness survey, consisting of interviews on the day of acute illness visit, day 10–14 from the first visit and day 28, if illness continues. The cost-of-illness survey questionnaire was designed to estimate the direct medical, direct non-medical and indirect costs associated with dengue-positive patients identified at study facilities. This survey also estimates the cost of treating dengue at the facility level. Data were gathered by linking patients’ medical records concerning outpatient visits, inpatient visits and service consumption (eg, diagnostic tests, medication and other services provided to patients). The cost-of-illness portion of the study will be described separately.

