### Study questionnaires

For the fever surveillance study, questionnaires were administered at the acute illness visit and the convalescent visit. The convalescent visit may take place at the healthcare facility (10–14 days later) or at the patient’s home (15–21 days after the acute visit), according to patient preference and availability. The questionnaires were completed by medical staff of the study facilities, including demographic and clinical information (eg, signs, symptoms, past medical history, treatments prescribed and diagnoses). The same staff also completed the follow-up questionnaire at the convalescent visit within 21 days from the acute visit. Study nurses completed surveillance enrolment log. Lab technicians completed the lab section (mostly dengue-related diagnostics) and the forms were compiled by the study coordinator on site.

For the serosurvey component, questionnaires were administered at the household by trained field team staff at each serosurvey visit. Study nurses completed the questionnaire after a brief physical and medical examination. At the follow-up visit(s) in about 6 months, the same staff made the household visits to complete the follow-up questionnaire. Enrolment log was maintained by the study coordinator on site.

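### RT-PCR on a small number of test-negative samples cannot exclude false negatives, and the incidence estimate makes no allowance for cases that the tests miss

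*Protocol article*

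**What the plan says.** Under Fever surveillance—design and methods, the article names two routes to confirmation: "Dengue confirmation was done by detection of dengue virus in serum samples using PCR as well as antidengue IgM and IgG antibodies", the antibodies being measured in acute and convalescent serum.

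The laboratory section describes three layers of testing:

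- On the day of presentation, "acute samples were tested using a commercial RDT for dengue NS1 and IgM/IgG".
- Next, "The acute and convalescent samples were subsequently tested at a local laboratory using dengue IgM/IgG ELISA".
- Last, "Samples with positive results by RDT or ELISA, as well as a small number of samples with negative results, undergo further testing by RT-PCR".

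The Figure 6 legend words the last step more loosely: "Selected samples, including those that were found positive by IgM and NS1 on Dengue Duo", together with ELISA positives. The Figure 5 legend gives the reason for including negatives: "A small number of those samples that are negative on ELISA or NS1 are tested with PCR to exclude false negative results of the ELISA".

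On the second sample, Study questionnaires says: "The convalescent visit may take place at the healthcare facility (10–14 days later) or at the patient’s home (15–21 days after the acute visit").

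Planned statistical analysis adjusts the incidence numerator for febrile patients who seek care outside the study facilities and for refusals. The Discussion adds inverse probability weighting for the same two losses. Neither section mentions infections missed by the tests in enrolled patients.

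**The concern.** Whether a sample gets RT-PCR depends on the result of the tests that RT-PCR is meant to check. Positives are verified, while negatives are verified only in an unspecified small number. This is partial verification. It says little about sensitivity unless the verified negatives are a known random fraction of all negatives and their result enters an estimate.

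The wording in Figure 5 goes further and presents the check as ruling false negatives out. A reader of the results could then take the case count among enrolled patients as complete.

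At stake is the incidence of symptomatic dengue. Cases missed among enrolled patients lower the numerator, and neither planned adjustment restores them. If the share of patients without a convalescent sample differs between Ouagadougou, Lambaréné and Mombasa, so does the undercount, and comparison across sites is a stated aim.

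**Working it through.** The plan states no figure for this step, so there is none to reproduce. Two illustrations follow.

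**Inputs from the article**
- Enrolment ceiling of 3000 (Sample size).
- Rapid-test positivity of 33/379 = 8.7% in an earlier Ouagadougou study (Site selection), used only to set a scale.
- These give 3000 × 0.087 = 261 positive and 3000 − 261 = 2739 negative.

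**Inputs assumed, because the article gives none**
- m, the number of negatives tested by PCR.
- sa, the sensitivity of the acute tests: 0.60 to 0.90.
- sc, the share of the remaining cases caught by convalescent ELISA: 0.95.
- d, the share of patients without a convalescent sample: 10% to 30%. Sample size allows 10% to 20%, variable by site, for non-response or loss to follow-up. That allowance sizes the catchment population and is only a rough guide to d.

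**1. What a small sample of negatives can rule out.** If none of m randomly drawn negatives is PCR-positive, the exact one-sided 95% upper limit on the false-negative fraction is 1 − 0.05^(1/m).

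| m | Upper limit | × 2739 negatives | Relative to 261 detected |
|---|---|---|---|
| 30 | 9.5% | 260 | 1.00 |
| 50 | 5.8% | 159 | 0.61 |
| 100 | 3.0% | 81 | 0.31 |
| 200 | 1.5% | 41 | 0.16 |
| 300 | 1.0% | 27 | 0.10 |

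The limit holds only for a random draw, and only for infection that PCR itself would detect.

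**2. How many cases might be missed.** A case is missed if the acute tests fail and there is either no convalescent sample or a convalescent ELISA that also fails:

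missed share = d(1 − sa) + (1 − d)(1 − sa)(1 − sc) = (1 − sa)[d + 0.05(1 − d)]

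- Best corner (sa 0.90, d 0.10): 0.10 × (0.10 + 0.045) = 0.0145, about 4 of 261 true cases.
- Middle (sa 0.75, d 0.20): 0.25 × (0.20 + 0.04) = 0.060, about 16 cases.
- Worst corner (sa 0.60, d 0.30): 0.40 × (0.30 + 0.035) = 0.134, about 35 cases.

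With no convalescent sample at all, the missed share would be 1 − sa, or 10% to 40% (26 to 104 cases). Paired ELISA therefore removes most of the problem.

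The share of missed cases that lack a convalescent sample is d/[d + 0.05(1 − d)]: 0.10/0.145 = 69% at d = 0.10, and 0.30/0.335 = 90% at d = 0.30. The residual group is mainly these patients.

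**Site comparison.** Take sa = 0.60 at two sites, with d = 0.10 at one and 0.30 at the other. The missed shares are 0.40 × 0.145 = 0.058 and 0.134, and the ratio of detected fractions is 0.866/0.942 = 0.92. Two sites with equal true incidence would differ by about 8%. With sa = 0.90 the ratio is 0.9665/0.9855 = 0.98.

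**Symptom model.** Missed cases as a share of the non-dengue group: 4/(2739 + 4) = 0.1% to 35/(2739 + 35) = 1.3%.

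**The case against.** The strongest objection is that the algorithm does not rest on acute antibody alone. Every acute sample has an NS1 antigen test, which can detect infection before antibody rises, and RDT positives go on to PCR. Convalescent serum is then tested by ELISA, and the option of a home visit makes a second sample easier to obtain. PCR on positives suits confirmation and serotyping. This stands, and it is why the missed share is about 1.5% to 13% and not 10% to 40%.

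A second objection is that a condensed article may leave the number of negatives, the sampling list and the classification rules to the full protocol. This also stands. A reader might infer that the negatives are chosen non-randomly, or that patients without a convalescent sample are simply counted as non-dengue. The article says neither, and the point does not depend on either. It rests on what the article does state: the aim of excluding false negatives, and a list of numerator adjustments that does not include test sensitivity.

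Third, a correction from few tests would be very imprecise. One PCR-positive among 50 scales up to 2739/50, about 55 cases. The exact 95% interval of 0.05% to 10.6% runs from about 1 to 292 cases, against 261 detected. That rules out a weighted correction as the primary estimate, but not as a reported sensitivity analysis. Dropping patients without a convalescent sample from the main comparator could likewise bring in selection, since acute-positive cases need not return to be counted.

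**Conclusion.** The point holds in limited form. Verification by RT-PCR depends on the index result, the claim that it excludes false negatives cannot be met by a small sample, and incidence is adjusted for two other losses but not this one. Under the assumed sensitivities and return rates, about 1.5% to 13% of cases would be missed, mainly among patients negative on all acute tests without a convalescent sample. A difference between sites is possible, but the article gives no return rates from which to judge it.

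Two stronger readings are not supported. One is that early infections in general remain in the non-dengue group and pull the odds ratios toward 1: NS1 and convalescent ELISA catch many of them, and contamination of about 0.1% to 1.3% has little effect. The other is that some 159 cases would be lost: that figure is the most that 0 of 50 cannot rule out, not an expected loss.

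**What to change.** - Keep the number of PCR tests. Draw the negatives at random within site and by convalescent sample present or absent, favouring early-fever patients without one, with known sampling fractions.
- Weight the PCR-positive fraction back to all negatives and report it with its exact interval. Carry it into incidence as a sensitivity analysis or bound, leaving the primary estimate as planned.
- Keep the non-dengue comparator as planned. Add a sensitivity analysis that omits acute-negative patients with neither a convalescent sample nor PCR.
- In the Figure 5 legend, give the purpose as estimating the false-negative fraction.

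The materials are in place: fever onset is recorded (Table 1), serum is stored in four aliquots, and samples are shipped to the PCR laboratory after ELISA. The cost is a sampling list, a little more analysis, and a wide interval around the possible undercount. If the negatives have already been chosen, report how they were selected and claim no more than that selection allows.

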#### Serological survey—design and methods

While the facility-based fever surveillance studies provide estimates of the burden of medically attended dengue disease, evaluation of all DENV infections in a population—including subclinical and mildly symptomatic infections, which impact immune status—is needed to capture the overall impact of dengue. As part of the study package, population-based serological surveys were conducted in the same catchment population used for the fever surveillance. At each of the three sites in Africa, the serosurvey was conducted on a cohort of approximately 3000 randomly selected residents of urban and semiurban parts of Ouagadougou, Lambaréné and Mombasa. Without individual-level census information on all residents of Lambaréné and Mombasa, with help of community/village health workers, randomisation was done based on neighbourhoods (or defined areas for which the health workers/volunteers are responsible) as cluster units. As the community/village health workers are familiar with the villages and their residents, they are good entry points into the communities. With these health workers, the field team screened houses in the selected villages by knocking on doors of every 5–7 houses, depending on the household density per neighbourhood. Also, demographic information collected in previous research projects conducted in the same area was used as a guide, if available. In the case of the site in Ouagadougou, HDSS data were available and the EQUITE SANTE, a CIHR funded research programme of the University of Montreal, had set up a geographic information system database of houses in the study area. Using these data, households of potential enrolees of the serosurvey were preselected randomly and household visits were made in Ouagadougou. In the three sites, about 45% of the serosurvey samples were targeted to be collected from children 1 to 14 years of age, and 55% were targeted to be collected from adults between 15 and 55 years of age to reflect the age distribution of the general population of the area. Household-based enrolment was offered to the head of the household until the specific cap for the age-group was reached in Lambaréné and Mombasa.

Randomly selected subjects 1–55 years of age underwent phlebotomy (5 mL for children and 7 mL for adults) twice—before the rainy season and after the rainy season, at approximately 6-month intervals. The sera were evaluated using IgG indirect ELISA at baseline and after 6 months. The presence of dengue IgG antibodies at 6-month intervals will be used to estimate the level of occurrence of inapparent DENV infection and to calculate the rate of infection in the catchment population. Flow cytometry-based DENV neutralisation assays will be applied to a subset of samples to assess for presence of dengue neutralising antibodies and seroconversion over the 6-month interval. In addition to overall seroconversion, age-specific seroconversion estimates in the catchment population as well as the proportion of inapparent infections will be determined.

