### Study area and population

Burkina Faso, located in West Africa, has a population of 14 017 462. The country is mainly rural with about 29% of the population reported to be living in urban areas in 2014. However, Burkina Faso is urbanising rapidly and is positioned as the country with the fourth fastest urbanisation in the last 25 years.^27 28^ The capital, Ouagadougou, has a population of 2 741 128. The majority of the population live in urban settings. About 45% of the population are under 15 years of age.^29^ The city is divided into 12 districts and 52 sectors. Ouagadougou is the country’s largest city and the cultural and economic centre. The city is part of the Soudano-Sahelian area, with a rainfall of about 800 mm per year. The rainy season is from May to October, with a mean temperature of 28°C (82°F). The cold season runs from December to January, with a minimum average temperature of 16°C (61°F). During the hot season, which runs from March to May, the temperature can reach as high as 43°C (109°F).

The HDSS is in place in Ouagadougou. Ouaga-HDSS monitors a population of 81 717 residents; according to this surveillance system, the city population is very stable with a rate of migration of 4.1% and more than 80% of the inhabitants with ownership of their houses [20]. A map of the city and the study area is shown in figure 2.

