**Figure 3 F3:**
[figure not shown]
Map of the study area in Lambaréné, Gabon.

Kenya, located in East Africa, lies on the equator, covering 581 309 km^2^ (224 445 sq. mi), with a population of approximately 45 million people in 2014.^32^ Kenya generally has a warm and humid tropical climate but is diverse, ranging from the cooler climate around the capital city, Nairobi, to a hot and dry climate inland as well as a desert-like climate in the north-eastern regions along the border with Somalia and Ethiopia.^32^ The capital, Nairobi, is a regional commercial hub. The main industries include agriculture, exporting tea and coffee as well as the service industry.

Kenya is divided into 47 semiautonomous counties. Mombasa is the country’s second largest city after Nairobi and is located on the east coast of the country.^32^ Administratively, Mombasa is the capital of Mombasa County, which was formerly called Coast Province. This overall Coast region covers over 80 000 km^2^ in the south-eastern part of Kenya, constituting about 15% of the country’s land area, with a population of 3 325 307 residents.

The main economic driver of Mombasa is tourism and trading industry. Mombasa itself has a population of about 1.3 million with almost 50% of the population under 15 years of age.^29^ Increasingly, the population of the province lives in urban areas; at present about 45% live in Mombasa and other urban centres. The ‘long rains’ period begins around April and the ‘short rains’ period begins in October.^32^ Mean annual temperature ranges from 24°C to 27°C, but maximum temperature averages over 30°C between January and April.

Figure 4 shows the area of Mvita subcounty of Mombasa, which was the catchment area for the study in Kenya, with a catchment population of 74 735 residents. The map indicates the three facilities involved in the study.

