In addition, a Luminex-based multiplex immunoassay will be performed on a randomly selected subsample to assess for IgG to different flaviviruses.^43^ About 200 samples per bleed for four bleeds in Burkina Faso and two bleeds in Gabon will be tested. Detection of IgG against ZIKV and each of the four DENV serotypes will be performed on patient serum samples using an in-house microsphere-based multiplex immunoassay (arbo-MIA) at the Clinical Immunology Lab of IVI.^44 45^ The arbo-MIA is based on a mixture of microspheres covalently coupled with either DENV-1, DENV-2, DENV-3, DENV-4 or ZIKV recombinant antigens (E protein domain III) produced in Drosophila S2 expression system. Briefly, microsphere mixtures were sequentially incubated in the dark under constant shaking with a 1:400 dilution of patient serum samples, with 2 µg/mL antihuman IgG biotin-conjugated antibody (Jackson Immunoresearch, West Grove, Pennsylvania, USA) and with 2 µg/mL streptavidin-R-phycoerythrin conjugate (Life technologies). After the final incubation, the median fluorescence intensity (MFI) of each microsphere set is quantified using a BioPlex 200 instrument (Bio-Rad Laboratories, Hercules, California, USA). Samples are considered seropositive if the ratio of MFI values obtained for the viral antigen to the control antigen is superior to the defined cut-off. The cut-off of the MIA is determined for each viral antigen by receiving operating characteristic (ROC) curve analysis using well-characterised sera.

In Lambaréné, the enrolment bleed took place in November–December 2015, while the second blood collection occurred in May 2016. In Ouagadougou, the enrolment bleed took place in May–June 2015 with follow-up blood collections in December 2015, June 2016 and January 2017. In Mombasa, the enrolment bleed took place in May 2016 with the second blood collection in November 2016–February 2017.

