As outpatient disease accounts for the greater part of dengue disease burden, clinical profile of individuals with DENV infection will be characterised by the type of treatment (hospitalised vs outpatients) as well as by severity of the disease (severe vs non-severe by the 2009 WHO criteria).^46^ Classification is determined after the course of illness is completed (typically during the convalescent visit). Symptomatic dengue is classified as outpatient or hospitalised. Progression of dengue is recorded as DF, DHF I, DHF II, DHF III or DHF IV, and clinical patterns will be compared by the severity grade.^46 47^ These will be compared with results obtained from other DVI studies in Latin America (Colombia) and Asia (Thailand, Vietnam and Cambodia). Overall, comparisons will be made across Burkina Faso, Gabon and Kenya.

With the age-stratified sera that reflect the age distribution of the general population of the country, the serological survey sampling strategy ensures sufficient subjects to obtain precise age-specific estimates of seropositivity and seroconversion of the catchment area population. The seroconversion rate and change in the immune status will be determined by age group during the study period. The age-stratified serosurvey data will also allow calculation of the force of infection of dengue in the study population. After enrolment, there are subjects who drop out in the follow-up bleeds about 6 months later. Basic demographic information will be compared between those that completed participation and those with incomplete participation to check whether study subjects represent the catchment area population. Comparisons will be made among Burkina Faso, Gabon and Kenya.

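### The serosurvey's before-and-after-rains, 6-month description does not match the article's own bleed dates at Ouagadougou and Mombasa, so seroconversion needs a person-time denominator

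*Protocol article*

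**What the plan says.** All references are to the Protocol article.

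- **Serological survey—design and methods.** Participants gave blood twice, "before the rainy season and after the rainy season, at approximately 6-month intervals". The interval is then put to use: "The presence of dengue IgG antibodies at 6-month intervals will be used to estimate the level of occurrence of inapparent DENV infection" and to calculate a rate of infection. Neutralisation assays on a subset are to assess "seroconversion over the 6-month interval".
- **Study area and population.** For Ouagadougou: "The rainy season is from May to October". For Mombasa: "The ‘long rains’ period begins around April and the ‘short rains’ period begins in October". No end date is given for either Mombasa period, and no rainy season is given for Lambaréné.
- **Serological survey—laboratory testing.** Ouagadougou was bled in May–June 2015, December 2015, June 2016 and January 2017. Lambaréné was bled in November–December 2015 and May 2016. In Mombasa "the enrolment bleed took place in May 2016 with the second blood collection in November" 2016, continuing to February 2017.
- **Planned statistical analysis.** Seroconversion is to be determined by age group, and the paragraph on the serosurvey closes with "Comparisons will be made among Burkina Faso, Gabon and Kenya".

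**The concern.** The design section presents one schedule for all three sites: a bleed ahead of the rains, a bleed after them, and about six months between. If that held, the seroconversion proportion would be roughly the same quantity everywhere, namely the risk over one wet season.

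The dates show that it is not the same quantity. The baseline at two sites was not taken ahead of the rains, one site has four bleeds, and the Mombasa interval varies by about three months between participants. If the interval is treated as six months and the sites are then compared, differences in exposure time and season can be read as differences in transmission. This matters because the article lists comparison by site, on standardised methods, among its strengths. In addition, infections acquired early in the rains but before a late baseline can be counted as prior immunity instead of seroconversion.

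**Working it through.** **1. Interval lengths.** The inputs are the bleed windows in *Serological survey—laboratory testing*. Shortest is the end of one window to the start of the next. Longest is the start of one to the end of the next. Midpoint runs from window midpoint to window midpoint. One month is 30.4375 days.

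| Site and bleeds | Shortest | Midpoint | Longest |
|---|---|---|---|
| Lambaréné 1–2 | 4.0 | 5.5 | 7.0 |
| Ouagadougou 1–2 | 5.1 | 6.5 | 8.0 |
| Ouagadougou 2–3 | 5.0 | 6.0 | 7.0 |
| Ouagadougou 3–4 | 6.1 | 7.1 | 8.0 |
| Mombasa 1–2 | 5.1 | 7.5 | 9.95 |

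The article's figure of about 6 months is roughly reproduced for Lambaréné and Ouagadougou. It is not reproduced for Mombasa, where mid-May to mid-November is 6.0 months and mid-May to mid-February is 9.0 months.

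**2. Position relative to the rains.**

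- *Ouagadougou (season May–October).* The enrolment window, May–June 2015, is the first two months of the season, and June 2016 is the second month. Neither bleed precedes the rains. December 2015 and January 2017 do follow them. In the December 2015–June 2016 interval, mid-December to the end of April is about 4.5 of 6.0 months, so it is mostly dry season and is not a before-and-after-rains pair.
- *Mombasa (long rains from about April, short rains from October).* The May 2016 baseline is after the long rains began and before the short rains began. The second bleed opened in November, after the short rains began.
- *Lambaréné.* The seasonal label cannot be checked.

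**3. Effect of interval length on seroconversion risk.** For a person seronegative at baseline, with constant force of infection λ per year and t months between bleeds, risk = 1 − exp(−λt/12). The article gives no λ, so a range is assumed.

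| λ per year (assumed) | 6 months | 9 months | Ratio |
|---|---|---|---|
| 0.01 | 0.50% | 0.75% | 1.50 |
| 0.03 | 1.49% | 2.22% | 1.49 |
| 0.05 | 2.47% | 3.68% | 1.49 |
| 0.10 | 4.88% | 7.23% | 1.48 |

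The ratio is close to 9/6 = 1.5 throughout, so the choice of λ hardly matters.

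**4. Illustration between sites.** At midpoints, Mombasa to Lambaréné is 7.5/5.5 = 1.36. With the risk formula it is 1.35 to 1.36 over the same range of λ. This assumes that Mombasa's second bleeds were spread evenly over November–February, which the article does not say.

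**The case against.** The strongest reply is that the article nowhere commits to the faulty analysis. It says approximately six months, speaks of rates, and does not rule out individual person-time. The exact model is normally left to an analysis plan, which is not shown here. The closing sentence on comparisons also covers seropositivity and force of infection, and a force of infection derived from age-specific baseline seroprevalence would not depend on the bleed interval. All bleed windows are published, so a reader can see the differences.

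Much of this stands. A reader might infer that the plan fixes a crude six-month proportion and will compare it between sites. The text does not go that far, and the missing model is not itself a fault. What remains is that the article names the six-month interval as the basis for the infection rate and for seroconversion, and describes a schedule that its own dates contradict. An unseen analysis plan would not correct that.

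Two other strong readings also fail. A reader might infer that the bleeds at two sites fell inside the rains. In Ouagadougou two of the four fell after the season, and the first interval still spans most of it. For Mombasa no end of the rains is stated, so only a baseline taken after the long rains began is supported. A reader might also take 1.36 as the expected bias. It is the most extreme pair of sites, rests on evenly spread bleeds, and assumes constant transmission. If transmission is seasonal, the true distortion could be larger or smaller.

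**Conclusion.** The concern holds as a conflict between the stated schedule and the stated dates, with a consequence for how seroconversion is expressed.

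- **Certain from the text:** two Ouagadougou bleeds lie within the rains, that site had four bleeds, the Mombasa baseline followed the start of the long rains, and the Mombasa interval runs from about 6 to 9 months (just under 10 at the extreme).
- **Conditional on a constant force of infection:** about a 1.5-fold difference in risk between the earliest and latest re-bled Mombasa participants, taken at mid-month. Nine months is the upper end there, and the window midpoint is 7.5.
- **Illustrative only:** the Mombasa to Lambaréné ratio of about 1.36.

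The length problem is chiefly Mombasa's, since about six months roughly fits the other two sites. The change should be made before seroconversion is compared across sites. It does not call the baseline seroprevalence results into question.

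**What to change.** 1. Express seroconversion as a rate per person-time among participants seronegative at baseline, using each person's own bleed dates. A Poisson model with log person-time as offset would serve, as would an interval-censored model.
2. Base between-site comparisons of seroconversion on that rate, and state which season each interval covers. Annualising alone does not remove seasonal imbalance.
3. Report Burkina Faso by interval as well as overall.
4. In *Serological survey—design and methods*, correct the number of bleeds and the claim of a pre-rains bleed for Ouagadougou. For Mombasa, qualify both the seasonal wording and the six-month label.

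**Cost.** This is analysis and wording only. Individual bleed dates should already be on record, so no new data are needed. The price is scientific: the simple before-and-after-season interpretation becomes weaker.
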